#### **E. Randomization and Blinding**

Randomization was performed using a computer-generated random numbers table with a block size of 6 and a 1:1:1 ratio after stratification according to the type of surgery and age. Allocation was sequentially numbered and sealed in opaque

---

envelopes by the corresponding author. The anesthesiologists opened the envelopes 10 min before the emergence procedure. Because of the nature of the intervention, full blinding of all study personnel was not feasible. However, to minimize bias, we attempted to blind patients, practitioners (where possible), research assistants, and data analysts. It was not feasible to blind the PACU anesthesiologists and nurses. To achieve patient blinding, during the informed consent process, we described all interventions as anesthesia emergence positions, and we explained that depending on group allocation, patients may receive different emergence positions during anesthesia emergence. We additionally performed an analysis of blinding success of patients using Bang's Blinding Index.

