## H. Intervention

At the end of operation, patients were transferred from operating table to transfer bed, and their positions were adjusted according to the groups.

supine position group (group S): Patients were placed in supine position from the end of surgery to leaving PACU.

15-degree semi-recumbent position group (group F): Patients were placed in 15-

---

degree semi-recumbent position from the end of surgery to leaving PACU.

30-degree semi-recumbent position group (group T): Patients were placed in 30-degree semi-recumbent position from the end of surgery to leaving PACU.

The inclination angle was set precisely by an inclinometer (GeeLii 55157, Shanghai GeeLii International Trade Co., China)

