## **J. Measurements and Endpoints**

The primary outcome was the incidence of postoperative hypoxaemia in the PACU (defined as  $\text{SpO}_2 < 90\%$  for more than 10 seconds or  $\text{PaO}_2:\text{FiO}_2$  ratio below 300 mmHg). We also recorded the incidence of severe hypoxaemia ( $\text{SpO}_2 < 85\%$  for more than 10 seconds) and the time to first episode of hypoxaemia. Patients were continuously monitored real-time vital signs in the PACU using a Mindray BeneVision N15 monitor (Shenzhen Mindray Bio-Medical Electronics Co., Ltd.). In this study, data collection was performed by one-on-one researchers in the PACU, review of the monitor's database by the data collector when the patient leaving the PACU. To avoid pulse oximeter probe dislodging the finger or having it only partially on the finger, we used disposable finger probes that stick to the finger like a Band-Aid for continuous monitoring (Disposable  $\text{SpO}_2$  Sensor, Shenzhen Mindray Bio-Medical Electronics Co., Ltd.).

The secondary outcomes included:

airway rescue (defined as the need for mask noninvasive positive pressure ventilation, or re-intubation);

respiratory symptoms (coughing);

extubation time (defined as the time from end of surgery to extubation);

respiratory comfort (before leaving PACU, graded using a numerical rating scale, ranging from 0 to 10, higher score means more comfort);

duration of stay in the PACU;

wound pain (VAS score measured at rest, while coughing at 5 and 30 minutes after extubation, before leaving PACU, and 24 hours post operation);

and position-related adverse events (hypotension, arrhythmia, and some other adverse events).

The patient's vital signs (heart rate and mean arterial pressure) were recorded at six time points: (1) the beginning of surgery (T0); (2) the end of surgery (T1); (3) immediately after adjusting position (T2); (4) immediately prior to extubation (T3); (5) 1 min after extubation (T4); (6) when leaving the PACU (T5).

Dynamic lung compliance ( $\text{C}_{\text{dyn}}$ ) and driving pressure ( $\Delta P$ ) were also recorded at

---

320 three time points: (1) when stitching; (2) 5 minutes after adjusting position; and (3)  
321 before extubation.

322 Arterial blood gas analysis was performed at three time points: (1) when stitching; (2)  
323 5 minutes after adjusting position; (3) 5 minutes post-extubation.

324

---

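### The PACU researchers who ascertain the primary outcome can probably see the allocated position, but Section E does not list them among the staff who could not be blinded

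*Protocol*

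**What the plan says.** Protocol Section E (Randomization and Blinding) concedes a general limit: "Because of the nature of the intervention, full blinding of all study personnel was not feasible". It then sets out what was tried: "we attempted to blind patients, practitioners (where possible), research assistants, and data analysts". One group is named as out of reach: "It was not feasible to blind the PACU anesthesiologists and nurses". Success of blinding is checked with Bang's index, for patients only.

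Section H (Intervention) fixes the position for the whole PACU stay. For the control arm: "Patients were placed in supine position from the end of surgery to leaving PACU". For the steepest arm: "Patients were placed in 30-degree semi-recumbent position from the end of surgery to leaving PACU". The 15-degree arm has the same duration.

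Section J (Measurements and Endpoints) states the endpoint: "The primary outcome was the incidence of postoperative hypoxaemia in the PACU". A patient counts as an event if SpO2 is below 90% for more than 10 seconds, or if the PaO2:FiO2 ratio is below 300 mmHg. On who records it, the section says "data collection was performed by one-on-one researchers in the PACU", followed by "review of the monitor's database by the data collector when the patient leaving the PACU".

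**The concern.** The primary outcome is observed in the PACU, and throughout that stay the patient lies in the allocated position. A researcher assigned to one patient there can hardly fail to tell supine from 30 degrees; 15 degrees is less obvious but still visible. Yet a reader of Section E, seeing one stated exception and finding research assistants among those for whom blinding was attempted, would take it that outcome data were collected by people kept unaware of the arm.

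Two things are at stake. The report could describe the masking of outcome collection more favourably than the procedures allow. And where reading the monitor record leaves room for judgement, such as whether a short dip meets the 10-second criterion or is a genuine signal, that judgement could differ between arms. Section J recognises poor probe contact as a source of error but gives no rule for handling a doubtful trace. Coughing, respiratory comfort and pain scores are more open to observer influence than SpO2.

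**Working it through.** **Setting the sections side by side**

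1. Position is held from the end of surgery until PACU exit (Section H).
2. The primary outcome arises between those two points (Section J).
3. Data are collected one-on-one in the PACU, and a data collector reviews the monitor database at exit (Section J).
4. No screening of the bed, separate masked assessor or remote reading of the record is described.
5. The staff named as not blindable are PACU anesthesiologists and nurses; data collectors are absent (Section E).

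The protocol never says whether the one-on-one researchers are the research assistants, so both cases need checking. If they are, the attempt to blind them could hardly succeed under the described procedure. If they are not, a probably unblinded group ascertains the primary outcome and is missing from Section E. The gap exists either way.

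**The plan's own figure (background only)**

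Section F gives 46% in the supine group, 34% in the combined tilted groups, 2:1 allocation, two-sided 5%, 80% power and continuity correction. With r = 2 and mean proportion (0.46 + 2 × 0.34)/3 = 0.38:

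- Uncorrected n (supine) = [1.960 × √(1.5 × 0.38 × 0.62) + 0.842 × √(0.46 × 0.54 + 0.34 × 0.66/2)]² / 0.12² = 193.8, so 194, or 582 in total.
- Corrected n = (193.8/4) × [1 + √(1 + 6/(193.8 × 2 × 0.12))]² = 206.1, so 207, or 621 in total.

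The stated 620 is reproduced. The blinding point does not depend on it; only the 46% and the 12-point difference are used below.

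**Possible size of the bias**

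Inputs: p = 0.46 in every arm (no true effect; rate from Section F); d = 0.10, the share of SpO2-only events in the tilted arms dismissed (assumed, not in the documents); s, the share of events that rest on SpO2 alone (not given, so a range is shown). A patient who also meets the PaO2:FiO2 criterion stays an event whatever happens to the SpO2 reading.

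Spurious gap = p × s × d

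| s | Gap | Share of the 12-point difference |
|---|---|---|
| 0.25 | 0.46 × 0.25 × 0.10 = 0.0115 (about 1.2 points) | 10% |
| 0.50 | 0.46 × 0.50 × 0.10 = 0.023 (2.3 points) | 19% |
| 1.00 | 0.46 × 1.00 × 0.10 = 0.046 (4.6 points) | 38% |

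For the combined-versus-supine comparison used for sizing, with 413 against 207 patients and an uncorrected normal approximation, the bottom row works out as follows. The pooled proportion is (207 × 0.46 + 413 × 0.414)/620 = 0.429. The null standard error is √(0.429 × 0.571 × (1/207 + 1/413)) = 0.0422, so the critical difference is 1.96 × 0.0422 = 0.0826. The standard error under the gap is √(0.46 × 0.54/207 + 0.414 × 0.586/413) = 0.0423. The upper tail is Φ((0.046 − 0.0826)/0.0423) = Φ(−0.87), about 0.19, and the lower tail adds about 0.001. The nominal 5% error therefore becomes about 19%. The same steps give about 8% for a 2.3-point gap and about 6% for a 1.2-point gap.

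**The case against.** A reader might infer that the protocol claims blinded outcome assessment and flatly contradicts itself. The text does not go that far. Section E speaks of an attempt, made after admitting that full blinding was not feasible, and nowhere asserts that assessment was masked. The research assistants, the one-on-one researchers and the data collector are never equated, nor is it said that the person reviewing the database is the one who attended the patient. That these people see the position is an inference from Sections H and J, though a strong one. All of this stands, and it limits the point to an incomplete and probably misleading account of who was unblinded.

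It is also fair to say that the endpoint is fairly objective. The thresholds are numeric, the monitor stores a record, adhesive probes were chosen to prevent dislodgement, and an arterial sample 5 minutes after extubation supports the second component. Section J describes no step in which a collector rejects a dip as artefact, so biased rejection is a possibility and not a documented practice. This stands as a limit on the size of the bias. It does not remove the exposure, because the protocol does not say how the 10-second criterion is applied to the stored record or how doubtful readings are handled, and it leaves the review to a data collector.

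The statistical analysis plan is not at hand, but who collects the data and who was blinded are conduct matters that this protocol already addresses, and the mismatch lies within its own sections.

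**Conclusion.** The point holds in a limited form. The people who ascertain the primary outcome are probably aware of the allocated position, and Section E does not list them as unblinded. Any discretion in reading the SpO2 record is therefore open to influence by knowledge of the arm.

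The documents do not show that bias occurred, in which direction, or how large it would be. A reader might take 4.6 points as the expected distortion. It is the upper end at an assumed 1-in-10 dismissal rate, reached only if every event rests on SpO2 alone. With half or a quarter of events of that kind, the gap is 2.3 or about 1.2 points. Both the dismissal rate and the SpO2-only share are assumptions. The matter merits correction because the remedy is cheap and the outcome is the primary one; it does not by itself discredit the result.

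**What to change.** 1. **Section E.** State that the PACU data collectors were not blinded. If some were, say which, and make clear how the research assistants relate to the one-on-one researchers and the data collector in Section J.
2. **Section J.** Derive the SpO2 component of the primary outcome, and severe hypoxaemia, from the stored monitor record at the resolution it holds. Apply the protocol's own thresholds (below 90%, and below 85%, for more than 10 seconds) and one artefact rule stated in advance. Files should carry the study number only, and the analyst running the rule should be unaware of allocation. Because Section E says only that blinding of analysts was attempted, the text should say how this was secured.
3. **Observer-dependent secondary outcomes.** Report coughing, respiratory comfort and pain scores as collected by unblinded staff. The algorithm does not help these.

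The cost is a data export and a short script, using a database that already exists and analysts the plan already intends to blind. It depends on the record having been kept and being exportable, which the protocol does not confirm. If it is not, items 1 and 3 can still be done, and the report should state that the SpO2 events were ascertained without blinding.

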#### **F. Sample Size Calculation**

The sample size for the primary outcome of this study was calculated with continuity correction, and was based on a ratio of exposed (combined 15-degree and 30-degree SRP) to unexposed (supine positioning) groups of 2:1. According to our pilot study, the frequency of hypoxaemia was 46% in the unexposed group, with a 26% relative (12% absolute) reduction in the exposed group. Assuming a two-tailed type I error rate of 5%, a sample size of 620 was needed to give greater than 80% power to detect a decrease in the incidence of hypoxaemia from 46% in the supine positioning group to 34% in the combined 15-degree and 30-degree SRP groups. Finally, we planned to recruit 700 patients to compensate for dropouts. The sample size calculation was conducted using the PASS 11.0 software (NCSS LLC).

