### C. Preliminary Studies

Currently, only a few studies have focused on the position during anesthesia emergence. Although there is no evidence to support a universal patient position for extubation, most anesthesiologists prefer to place patients in supine position. This is because it is simple, and enables easy observation. However, the reduction in functional residual capacity (FRC) caused by the supine position tends to promote airway closure and reduce gas exchange. Although, there is a growing preference for anesthesia emergence in semi-recumbent position. However, there is still a lack of reliable clinical evidence to demonstrate its efficacy, safety, and appropriate tilt angle. Therefore, we hypothesized that putting patients undergoing laparoscopic upper abdominal surgery in a semi-recumbent position during anesthesia emergence can reduce the incidence of postoperative hypoxemia.

---

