#### **G. Statistical Analysis**

Continuous variables were presented as mean (SD) or median (interquartile range, [IQR]), depending on whether the data was distributed normally or not. Categorical variables were presented as a number (percentage). The normal distribution of data was evaluated using the Shapiro–Wilk test, and the Levene method was used to test the homogeneity of variance. Differences in repeated measures variables were analysed by repeated-measures analysis of variance. Continuous outcomes were

analysed with one-way analysis of variance (ANOVA) or Kruskal-Wallis test. Categorical variables were tested using  $\chi^2$  test or Fisher's exact test. The primary analyses were performed according to the intention-to-treat (ITT) principle. Modified ITT (mITT) and per-protocol (PP) analyses were also performed as sensitivity analyses for the primary outcome. Results of primary and secondary outcomes were reported as relative risk (RR) or between-group difference with 95 % CI, the absolute risk reduction (ARR) and Number needed to Treat (NNT) were also calculated, with 95% CI. Kaplan-Meier curves were used for the time to first experience hypoxaemia. When an overall intervention effect was detected ( $P < 0.05$ ), the Bonferroni correction for multiple pairwise comparisons would be performed. To handle missing data, multiple imputations by chained equations was used, assuming missing data are missing at random. Imputation for continuous data was performed by predictive mean matching, logistic regression for binary variables. The number of imputations was 5. Convergence of the multiple imputation algorithm and the results of the imputation were checked. Imputations were performed with the R MICE package (J Stat Software. 2011;45(3):1–67.). Analyses were then performed on each of the imputed data sets and pooled according to Rubin's rules. As a post hoc sensitivity analysis, we used a logistic regression model simultaneously entering: age, BMI, current smoking status, chronic pain needing opioids, ARISCAT score (Assess Respiratory Risk in Surgical Patients in Catalonia), CCI (Charlson Comorbidity Index), surgery time, intraoperative opioid consumption, and the use of a nasogastric tube. R version 4.1.1 was used for statistical analysis, and analysis items with 2-sided  $P < 0.05$  were considered statistically significant.

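### The stated power above 80% belongs to supine versus the combined tilted arms, a contrast that the analysis section never names as the primary test

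*Protocol*

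**What the plan says.** Section E (Randomization and Blinding) allocates three arms 1:1:1. Section F sizes the primary outcome on a single two-group contrast: the calculation "was based on a ratio of exposed (combined 15-degree and 30-degree SRP) to unexposed (supine positioning) groups of 2:1". The assumed risks run "from 46% in the supine positioning group to 34% in the combined 15-degree and 30-degree SRP groups", and the result is stated as follows: "Assuming a two-tailed type I error rate of 5%, a sample size of 620 was needed to give greater than 80% power". Recruitment is raised to 700 for dropouts.

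Section G lists chi-square or Fisher's exact tests for categorical variables and one-way ANOVA or Kruskal-Wallis for continuous ones. It makes Bonferroni-corrected pairwise comparisons conditional: "When an overall intervention effect was detected", at P < 0.05. It does not say how many pairs are counted. No sentence in section G pools the two tilted arms or compares them jointly with supine.

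The title and section I ask about different degrees of tilt. Section II.C says reliable evidence is lacking "to demonstrate its efficacy, safety, and appropriate tilt angle", and then states a hypothesis about semi-recumbency in general, without naming an angle.

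**The concern.** Power is a property of a particular test. Section F computes it for a one-degree-of-freedom comparison. Section G describes an overall test followed by pairwise tests and does not say that the overall test is the one powered in section F. For three parallel arms the usual reading of that sequence is a 3×2 chi-square followed by pairs. The use of ANOVA and Kruskal-Wallis for continuous outcomes points the same way.

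Two things are at stake. First, the pooled test and the three-group test can reach different verdicts on the same data. If the choice between them is left open until the results are seen, the 5% error rate for the primary outcome is not protected. Second, what the title asks about individual angles rests on the pairwise tests, for which no power is stated. A non-significant result for one angle could be taken as evidence that it does not work, when the test had little more than an even chance of detecting the planned effect.

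**Working it through.** **Inputs.** From section F: supine risk p₁ = 0.46, combined tilted risk p₂ = 0.34, difference d = 0.12, ratio k = 2, two-sided α = 0.05, continuity correction, N = 620 (recruitment 700). From section E: 1:1:1, so m = 206.7 per arm at 620 and 233.3 at 700. Assumed, because the protocol gives no risk for each angle: 34% at both angles, with a range below. Also assumed, because section G gives no number: three or two Bonferroni pairs.

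**1. The plan's own figure.** The average risk is p̄ = (0.46 + 2×0.34)/3 = 0.38.

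n₀ = [1.960·√((k+1)p̄(1−p̄)) + 0.842·√(k·p₁(1−p₁) + p₂(1−p₂))]² / (k·d²) = 193.8 in the supine arm (581 in total).

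With continuity correction: n = (n₀/4)·[1 + √(1 + 2(k+1)/(n₀·k·d))]² = 206.1, total 618. Rounding the supine arm up to 207 gives 621. So 620 reproduces.

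Power at 620: the null SE is √(0.38×0.62×1.5/206.7) = 0.0414, the alternative SE is 0.0418 and the correction is 0.0036. Then (0.12 − 0.0036 − 1.960×0.0414)/0.0418 = 0.85, which is 80.1% (82.4% without correction). At 700 it is 84.9% (86.7%).

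**2. Three-group chi-square, 2 df.** The noncentrality is λ = m·Σ(pᵢ − p̄)²/[p̄(1−p̄)]. If the angles have risks 0.34 ± δ, the sum is 0.08² + (δ−0.04)² + (δ+0.04)² = 0.0096 + 2δ². It is smallest at δ = 0, so equal benefit is the worst case for this test at a fixed 34% average. At 620 with δ = 0, λ = 206.7×0.0096/0.2356 = 8.42. The critical value is 5.99.

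| Risks in the tilted arms | λ at 620 | Power at 620 | Power at 700 |
|---|---|---|---|
| 34/34% | 8.42 | 74% | 79% |
| 36/32% | 9.12 | 78% | 83% |
| 37/31% | 10.0 | 82% | 86% |
| 40/28% | 14.7 | 94% (95% simulated) | 96% (97% simulated) |

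**3. Each angle against supine, 46% versus 34%.** The pair average is 0.40. At 620 the null SE is √(0.40×0.60×2/206.7) = 0.0482 and the alternative SE is 0.0478.

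- Three pairs, α = 0.0167: (0.12 − 2.394×0.0482)/0.0478 = 0.10, power 54%; 60% at 700.
- Two pairs, α = 0.025: (0.12 − 2.241×0.0482)/0.0478 = 0.25, power 60%; 66% at 700.

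These allow no continuity correction; with it they are 50% and 56% at 620. Simulating the full sequence, including the overall gate, gives 54% for three pairs and 58–59% for two at 620, and about 60% and 65–66% at 700. Both angles are significant in about 38% of trials at 620 with three pairs. If the angles differ, the weaker one fares worse: with three pairs, about 29% at a risk of 37% and 12% at a risk of 40%.

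**4. Does the choice of overall test matter?** In simulated trials at 207 per arm with 46/34/34%, the pooled test alone is significant in 9.8% and the three-group test alone in 1.1%, so the verdicts differ in about 11%. With 46/40/28% they differ in about 14%, mostly with only the three-group test significant.

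**The case against.** The best defence is that the pooled contrast is already the intended primary test. Section F ties it to the primary outcome at two-sided 5%, and the hypothesis in section II.C does not depend on the angle. A chi-square or Fisher test fits a 2×2 pooled table as well as a 3×2 one. On this reading the overall effect is supine versus combined, the angle tests follow, and the stated power is right. The phrase about tilt angle in section II.C describes a gap in the literature and is not a stated hypothesis. The exact table layout is also commonly left to an analysis plan, and none is shown here.

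Much of this stands. A reader might infer that the plan performs a three-group test and that its stated power therefore belongs to none of its tests. The protocol does not support that: section G never says three-group, and the pooled reading is possible. A reader might also infer that a three-group test would always fall below 80%. That fails too, since 37/31% gives about 82%. Nor is 620 a wrong figure, and follow-up comparisons behind a gate are not required to have 80% power.

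What remains is that section G does fix a testing sequence, and it does not identify the overall test as the contrast that section F powered. The low power of the angle comparisons is the same on both readings.

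**Conclusion.** The concern holds as a failure to connect sections F and G on the primary test. The power above 80% is correct for supine versus the combined arms and for nothing else, and section G does not name that contrast. If the overall test is the three-group test, its power at 620 is about 74% under equal benefit, and more if the angles differ. On either reading each angle against supine has about 54–59% power at 620 and 60–66% at 700, depending on whether three or two pairs are counted. These figures assume 46% in the supine arm and 34% at both angles, and at 700 that every recruited patient is analysable. They describe what the design can detect under its own assumptions; they do not show that the sample size is in error.

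**What to change.** In section G, name supine versus the combined 15- and 30-degree arms as the single primary test of the primary outcome at two-sided 5%. Only if it is significant, test each angle against supine at Bonferroni 0.025 each.

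In section F, say that the power above 80% applies to the pooled contrast only, and add that each angle comparison has about 59% power at 620 (about 65% at 700), assuming 34% at both angles.

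If the three-group test is preferred as primary, say so in section G and restate its power in section F as about 74% at 620 (79% at 700) under equal benefit at both angles, higher if they differ. Also state how many pairs the Bonferroni correction covers.

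The cost is a few sentences and no extra patients. The stated power for the angle-specific questions becomes less favourable. A pooled primary test also gives up some power if the angles differ sharply: about 83% against 95% for the three-group test at 40/28%, both simulated without continuity correction.
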